### 10.2 Sample Size Considerations

At least 15,000 patients (~1 year of data), and no more than 45,000 patients (~3 years of data), will be randomized 1:1 to the intervention or control arms. If we assume an overall median risk of 1%, we will achieve 80% power to detect a risk reduction from

1% to 0.595% if there are at least 7500 subjects per group. We are aware that due to the low baseline event rate, we may need to enroll additional patients to achieve the necessary power. This will be the largest randomized controlled trial ever performed to answer this important question in pediatrics and will therefore be an important contribution to the literature both for pediatric hematology and in the field of pediatrics.

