## 2.2 Model Development

We evaluated data from 111,352 admissions to Vanderbilt Children's Hospital from 1/1/2010 to 10/31/2017. Cases were identified from ICD9/10 codes and a subset of these records were reviewed for accuracy. Potential covariates were identified from known pediatric risk factors for VTE development prior to data collection, and the corresponding clinical data were electronically extracted through the Vanderbilt Research Derivative. Logistic regression was used to test the association of potential risk factors with development of VTE. Variable inclusion in the final model was based on data reduction methods including univariate analysis significance, availability in routine medical records, clinical expertise, and assessment of collinearity between variables. The model was validated using an internal bootstrap calibration.

We identified 110,537 controls and 815 cases within the cohort. The most significant variables for developing VTE were a history of thrombosis (OR 8.7, 95% CI 6.6 – 11.3,  $p < 0.01$ ), presence of a central venous line (OR 4.9, 95% CI 4.0 – 5.8,  $p < 0.01$ ), and cardiology consultation (OR 4.0, 95% CI 3.3 – 4.8,  $p < 0.01$ ). Additional significant variables included whether a blood gas was performed, whether the patient had an infectious diseases consultation, patient age, mean corpuscular hemoglobin concentration (MCHC), red cell distribution width (RDW), and lactate. We selected these 11 final variables for use in the model, which yielded excellent discriminatory power (C-statistic = 0.907 in the model development cohort).

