## 10 Statistical Considerations

### 10.1 Statistical Analysis Plan

Primary analyses will be conducted at the encounter level, while secondary analyses will be conducted at the patient level (patients can potentially experience multiple encounters during the study period).

The rate of VTE events (primary outcome), the proportion of patients receiving prophylactic anticoagulation (secondary outcome), and the rate of bleeding-related adverse events (secondary outcome) will be compared between the intervention and control arms using unadjusted risk differences with 95% confidence intervals. We have not specified *a priori* any adjustment variables to include in multivariable models. Any variable with a clinically meaningful imbalance between the intervention and control groups will be adjusted for in multivariable regression models; given the large sample size we do not anticipate any such imbalances. For the primary outcome, a two-sided p-value (obtained from Pearson's chi-square test) of  $< 0.05$  will indicate statistical significance. Secondary subgroup analyses will be performed by patient gender, risk of VTE, primary diagnoses, surgical vs. nonsurgical, and consultants involved.

Primary analyses will be conducted by intention-to-treat; secondary analyses will be as treated, considering whether treatment recommendations were followed by the admitting team. Secondary as-treated analyses will be performed among the strata of high-risk patients (predicted probability  $\geq 0.025$ ) randomized to usual care, to the intervention but treatment recommendations were not followed, and to the intervention and treatment recommendations were followed.

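### The 80% power in section 10.2 rests on an unsourced 1% median risk; at the protocol's own cohort rate of 0.73%, and with the same relative reduction, power at the 15,000 minimum is about 66%

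*Protocol*

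**What the plan says.** Section 10.2 of the protocol sets total enrolment between 15,000 and 45,000, allocated 1:1. Its only power statement opens with "If we assume an overall median risk of 1%, we will achieve 80% power to detect a risk reduction from". The reduction it names ends at a risk of 0.595%, and the size it requires is 7,500 per arm or more. It then says that, because events are rare, more patients may have to be enrolled to reach the needed power. Section 12 likewise lets enrolment run from one to three years.

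Section 10.1 names the primary test: "a two-sided p-value (obtained from Pearson's chi-square test", at the 0.05 level. Sections 6.5 and 10.1 make the hospital encounter the unit of the primary outcome and its analysis.

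Section 2.2 describes the hospital's own data behind the risk model: "We evaluated data from 111,352 admissions" and "We identified 110,537 controls and 815 cases within the cohort".

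**The concern.** Two figures for the baseline VTE risk at this hospital stand in the protocol and are never reconciled. The power statement uses 1%. The cohort gives about 0.73%, roughly a quarter lower, in the unit that the primary endpoint uses.

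The 1% is also described as a median. The power of a chi-square test on two proportions is set by the proportion with an event, which is the mean of the individual risks. A median risk is a different quantity and does not belong in this calculation.

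At stake is the one power figure that the trial offers. The protocol allows enrolment to end at 15,000, and 80% is claimed for that size. If the control rate is nearer 0.73% and the intervention works as well in relative terms as planned, a null result at the minimum would be read as better powered than it was.

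**Working it through.** **Inputs**
- Section 10.2: control risk 1%, intervention risk 0.595%, 7,500 per arm, 1:1. The implied relative risk is 0.00595/0.01 = 0.595, a relative reduction of 40.5% and an absolute drop of 0.405 percentage points.
- Section 10.1: two-sided Pearson chi-square test at 0.05.
- Section 2.2: 815 cases and 110,537 controls, 111,352 admissions.
- Section 9: withdrawals are not anticipated, so no inflation for dropout.

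**Formula.** With p1 and p2 the two risks, p̄ their average and n the number per arm:

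SE0 = √[2p̄(1−p̄)/n], SE1 = √{[p1(1−p1) + p2(1−p2)]/n}, power = Φ[(|p1−p2| − 1.96·SE0)/SE1].

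**Step 1: the plan's own figure.** p1 = 0.01, p2 = 0.00595, n = 7,500. SE0 and SE1 are both 0.001452 to four figures. z = (0.00405 − 1.96 × 0.001452)/0.001452 = 0.83, so power = 79.6%. Exact enumeration of the chi-square test gives 80.2%. The formula needs 7,571 per arm for 80%. The stated figure reproduces.

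**Step 2: the cohort rate.** 815/111,352 = 0.00732, or 0.73% per admission. The approximate 95% interval is 0.00732 ± 1.96 × √(0.00732 × 0.99268/111,352), that is 0.68% to 0.78%. Sampling error in the cohort does not stretch to 1%.

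**Step 3: power at the cohort rate, relative reduction held at 40.5%.** p1 = 0.00732, p2 = 0.595 × 0.00732 = 0.00435, n = 7,500. SE0 and SE1 are both about 0.001244. z = (0.00296 − 1.96 × 0.001244)/0.001244 = 0.42, so power = 66.4%. Exact enumeration gives 66.9%.

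**Step 4: power at 7,500 per arm over a range of control rates, same relative reduction.** The rates other than 1% and 0.73% are illustrative assumptions.

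| Control rate | Intervention rate | Power |
|---|---|---|
| 1% | 0.595% | about 80% |
| 0.85% | 0.506% | about 73% |
| 0.73% | 0.435% | about 66% |
| 0.6% | 0.357% | about 58% |

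**Step 5: what would restore 80% at 0.73%.**
- With n fixed at 7,500 per arm, p2 must fall to about 0.390%: 1 − 0.390/0.732 = 47% relative reduction.
- With the 40.5% reduction fixed, n = 10,366 per arm, or about 20,700 in total.
- At the 45,000 cap (22,500 per arm), power for the 40.5% reduction is about 98%.

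**Step 6: sensitivity to which effect is held fixed.** If the absolute drop of 0.405 points is kept instead, p2 = 0.732% − 0.405% = 0.327%. Power at 7,500 per arm is then about 93%, but the relative reduction becomes 0.405/0.732 = 55%.

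**The case against.** **The 80% is conditional and correct on its condition.** This stands. Section 10.2 says what it assumes, and the figure follows. A reader might infer a calculation error, but there is none.

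**The 66% depends on holding the relative reduction.** This stands as a condition to be stated. Section 10.2 gives two absolute risks, and section 10.1 reports risk differences, so the protocol does not commit itself to a relative effect. Keeping the absolute drop gives about 93%. That requires a 55% relative reduction, which the protocol nowhere claims. Holding the relative effect is the usual choice when a baseline rate falls.

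**The protocol already foresees the problem.** This stands in part. It warns that more patients may be needed, 15,000 is only a floor, and about 20,700 lies well inside the permitted range. But the caveat gives no revised rate and no target, and the 80% attached to 7,500 per arm is left as it was.

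**0.73% may not be the trial's control rate.** This stands. The cohort covers 2010 to 2017, with cases found by diagnosis codes and only a subset reviewed. The trial excludes patients on anticoagulants, which could lower the rate, and observation-status admissions, whose exclusion could raise it. It finds events through radiology reports as well as codes. A reader might infer that the true rate must lie below 0.73%, but the documents leave the direction open. It remains the best estimate in the protocol, and nothing there supports 1%.

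**The median may be only a slip of wording.** Also fair: the 1% was used numerically as an event proportion. Risk is probably right-skewed, since section 6.2 expects over 90% of patients to score below 2.5%, but no median score is reported. How far the median lies below the mean cannot be taken from the documents.

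**Conclusion.** The point holds as a conflict over an input. The only power figure in the protocol rests on an unsourced 1% that disagrees with the hospital's own 0.73% per admission, and it names the wrong summary of risk. At 0.73%, power at the 15,000 minimum is about 66% instead of 80%, so the chance of missing the planned effect rises from about 20% to about 34%.

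This rests on two assumptions: that the cohort rate approximates the trial's control rate, and that the relative reduction stays at 40.5%.

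A reader might go further and conclude that the trial as designed is underpowered. The documents do not support that: the enrolment range already contains the roughly 20,700 encounters needed and extends to about 98% power. What needs correcting is the claim made for the minimum size.

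**What to change.** Rewrite the power paragraph in section 10.2:

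- Replace the median risk of 1% with the expected VTE rate per encounter, based on the 0.73% in section 2.2, or give a reason for 1%.
- State that the relative reduction is held at 40.5%.
- Give power at 7,500 per arm over a range of rates: about 80% at 1%, 73% at 0.85%, 66% at 0.73% and 58% at 0.6%.
- Add that at 0.73% the effect detectable with 80% power at 7,500 per arm is a fall to about 0.39% (47% relative), and that 80% power for the 40.5% reduction needs about 20,700 encounters in total, which the existing range allows.
- Count encounters, the unit analysed, in place of patients or subjects.

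The cost is one paragraph of wording. Neither the enrolment range nor the analysis has to change. The downside is that the power stated for the minimum becomes less favourable.

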## **11 Privacy/Confidentiality Issues**

At no time during the course of this study, its analysis, or its publication will patient identities be revealed in any manner. Patient privacy will be maintained by only using the minimum necessary data containing patient or provider identities. Identifiable data will be used for initial chart review and recommendations. As quickly as feasible, all data collected will be uploaded into a password-protected computerized database maintained within a secure, web-based application for building and managing online databases (REDCap) or stored on secure servers with user-level access control. The data will then be de-identified prior to the statistical analysis. All data will be reviewed as group summary information to minimize potential patient identification by the reviewing group. All identifiers will be removed prior to publication. The identifiable data will not be used in any other research projects and will be destroyed after six years following initial publication.

## **12 Follow-up and Record Retention**

Enrollment for the study will last for a minimum of one year, although may run for up to three years in order to obtain sample size needed. For each participant, the study will commence at enrollment and study intervention will last until hospital discharge or in-hospital death. Patient clinical outcomes will be collected up until hospital discharge or death. Identified data in the secure database (REDCap) will be stored for up to three years following initial publication.

